## Abstract

**Background:**

Danhong injection (DHI) has been widely prescribed to patients with acute ischemic stroke (AIS). However, due to methodological deficiencies, previous research has not yet provided rigorous evidence to support the use of DHI in the treatment of AIS. Therefore, we designed this multicenter, randomized, controlled, and double-blind trial to evaluate the efficacy and safety of DHI for AIS.

**Methods/Design:**

It is a randomized, multicenter, double-blind, placebo-controlled, adaptive clinical trial. A total of 864 eligible patients will be randomized into either the DHI or placebo group in a 2:1 ratio. All patients will be given the standard medical care as recommended by guidelines. Participants will undergo a 2-week treatment regimen and 76-day follow-up period. The primary outcome is the proportion of patients with a favorable outcome, defined as a score of 0–1 on the modified Rankin scale at day 90. Secondary outcomes include a change in the total score of the Chinese medicine symptom scales of “*Xueyu Zheng*” (blood stasis syndrome), the proportion of patients with a Barthel Index score of ≥90, the proportion of patients with an improvement in NIHSS score of ≥4 or NIHSS score of 0–1, quality of life measured by the EQ-5D scale, etc. Safety outcomes such as global disability (mRS ≥3) at day 90 will also be assessed. The changes in mRNA and microRNA profiles in 96 patients selected from certain centers will also be assessed. As this is an adaptive design, two interim analyses are prospectively planned, which will be carried out after one-third and two-thirds of patients have completed the trial, respectively. Based on the results of the interim analyses, the Data Monitoring Committee (DMC) will decide how to modify the study.

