**Fig. 1 Fig1:**
[figure not shown]
The flow diagram of this trial

**Table 1 Tab1:** Data collection schedule and measures

Period	Run-in period	Treatment period		Follow-up period		
Day	0	7 ± 2	14 ± 2	30 ± 5	60 ± 5	90 ± 3
Informed consent	×					
Inclusion/exclusion criteria	×					
Medical history	×					
UCG	×					
TOAST	×					
Medical examination	×	×	×	×	×	×
Concomitant medications	×	×	×	×	×	×
Outcomes						
BI scale	×	×	×	×	×	×
mRS scale	×	×	×	×	×	×
NIHSS	×	×	×	×	×	×
Chinese medicine symptom scales of “*Xueyu Zheng*”	×	×	×	×	×	×
EQ-5D scale	×	×	×	×	×	×
Global disability on mRS						×
New-onset major vascular events						×
Overall mortality						×
Incidence of severe hemorrhages						×
Incidence of moderate hemorrhages						×
AEs and SAEs						×
Profiles of microRNA in 60 patients from certain centers	×		×			×
Profiles of mRNA in 60 patients from certain centers	×		×			×

*UCG* ultrasound cardiogram, *TOAST* Trial of Org 10 172 in Acute Stroke Treatment, *BI* Barthel Index, *mRS* modified Rankin Scale, *NIHSS* National Institutes of Health Stroke Scale, *AEs* adverse events, *SAEs* serious adverse events, *microRNA* micro-ribonucleic acid, *mRNA* messenger ribonucleic acid

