### Sample size estimation

The proportion of patients who had a favorable outcome, defined as a modified Rankin Scale (mRS) score of 0–1, after standard medical care coupled with placebo or DHI for 90 days was unclear. According to previous studies [10, 11], the proportion of patients who had a mRS score of 0–1 was about 28.7–45.2 % when only treated with placebo, so we estimate the proportion is 45 % when placebo coupled with standard medical care are used. In this trial, it is hypothesized that an increase of at least 10 % is of clinical significance for the DHI group. An adaptive design was selected and EAST5.2 software was used to calculate the statistical sample size. After calculation, the number of subjects was initially estimated to be 703 (one-sided test, α = 0.05, β = 0.2). To allow for a dropout rate of 20 %, a total of 846 patients will be recruited. According to the adaptive design, the sample size may be adjusted after the interim analyses, which will be carried out when one-third (282) and two-thirds (564) of patients have completed the trial, respectively. With a 2:1 randomization ratio, the number of participants in the DHI group is 564 and that in the control group is 282.

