#### Secondary outcomes

The total score of Chinese medicine symptom scales of “*Xueyu Zheng*” (blood stasis syndrome).The proportion of patients with the Barthel Index (BI) score of ≥90. BI uses ten variables to describe the activities of daily living (ADL) and mobility, and a higher number is associated with a better performance of ADL [14].The proportion of patients with an improvement in the NIHSS score of ≥4 or the NIHSS score of 0–1. NIHSS is a tool used to objectively quantify the impairment caused by stroke. A NIHSS score of 0 typically indicates normal function in that specific ability, while a higher score is indicative of some level of impairment [15].The quality of life measured by the EQ-5D scale. The EQ-5D scale has five standard dimensions to measure the generalized health-related quality of life [16].Global disability (mRS ≥3) at day 90.Incidence of new-onset major vascular events within 90 days. Major adverse vascular events include ischemic stroke, hemorrhagic stroke, transient ischemic attack, myocardial infarction and vascular-related death.The safety of DHI is evaluated by the incidences of global disability (mRS ≥3) at day 90, new-onset major vascular events, severe hemorrhages and moderate hemorrhages within 90 days. The definition of “severe hemorrhages” and “moderate hemorrhages” is in accordance with the GUSTO bleeding criteria [17]. Other safety measures include the overall mortality at day 90. All the adverse events (AEs) and serious adverse events (SAEs) within 90 days should be observed and documented. Other outcome measures include the changes in the mRNA and microRNA profiles in 60 patients selected from certain centers. An overview of the measurement data collection schedule is shown in Table 1.

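### The abstract's trial size (864) and RNA substudy size (96) contradict the methods (846 and 60) and should be reconciled

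*Protocol article*

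**What the plan says.** **Total size.** The Methods/Design paragraph of the abstract states: "A total of 864 eligible patients will be randomized into either the DHI or placebo group in a 2:1 ratio". In the body, Sample size estimation starts from 703 ("the number of subjects was initially estimated to be 703 (one-sided test, α = 0.05, β = 0.2") and continues: "To allow for a dropout rate of 20 %, a total of 846 patients will be recruited". The same section gives 564 patients to DHI and 282 to control, and puts the two interim analyses at 282 and 564 completers.

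**Interim fractions.** The abstract, Sample size estimation and Interim analysis all place the looks at one-third and two-thirds of patients.

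**RNA substudy.** The abstract states: "The changes in mRNA and microRNA profiles in 96 patients selected from certain centers will also be assessed". The Secondary outcomes section instead has "changes in the mRNA and microRNA profiles in 60 patients selected from certain centers". Table 1 has "Profiles of microRNA in 60 patients from certain centers" and a parallel row for mRNA, also with 60.

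**The concern.** Both pairs of figures stand in the current text. Neither comes from an amendment log.

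A trial's planned size is the benchmark for its final enrolment. That matters more than usual here, because the design allows early termination for superiority and re-estimation of the sample size at two looks. A later reader has to be able to tell a change made at an interim analysis from the original target, and two published targets blur that.

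For the substudy, Table 1 schedules the profiles at three time points (days 0, 14 and 90). The count therefore sets how many patients are profiled three times.

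**Working it through.** **Inputs** (all from Sample size estimation unless noted): control rate 45%; increase of 10 points, so 55% on DHI; one-sided α = 0.05; power 80%; allocation 2:1; dropout 20%; 703 before dropout. Interim analysis adds two looks with Lan-DeMets O'Brien-Fleming-type spending.

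**1. Reproducing 703.** With unpooled variance, the control arm needs

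n = [0.45 × 0.55 + (0.55 × 0.45)/2] × (1.645 + 0.842)² / 0.10² = 229.5,

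so the total is 3 × 229.5 = 688.6. The inflation for looks at 1/3, 2/3 and 1 under that spending function is 1.0203, and 688.6 × 1.0203 = 702.6, that is, 703. A fixed design with pooled variance gives 693. The stated 703 is reproduced.

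**2. From 703 to the total.**
- 703 × 1.2 = 843.6, rounded up to 844; the next multiple of 3 is 846, the methods figure.
- 703 / 0.8 = 878.75, rounded up to 879.
- 864 results from neither. Under the × 1.2 rule it would need 864 / 1.2 = 720 before dropout, and 720 appears nowhere.

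**3. Consistency with the other counts.**

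| Quantity | From 846 | From 864 | Stated in the body |
|---|---|---|---|
| DHI arm (2/3) | 564 | 576 | 564 |
| Control arm (1/3) | 282 | 288 | 282 |
| First look (1/3) | 282 | 288 | 282 |
| Second look (2/3) | 564 | 576 | 564 |

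The gap is 864 − 846 = 18 patients (18/846 = 2.1%): 12 on DHI and 6 on control. The looks would move by 6 and 12 completers.

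**4. Effect on power.** After 20% loss, 846 leaves 676.8 patients and 864 leaves 691.2. Using the design that reproduces 703, power ≈ Φ(2.486 × √(N/702.6) − 1.645):
- 846: Φ(2.486 × 0.9815 − 1.645) = Φ(0.796) = 78.7%.
- 864: Φ(2.486 × 0.9919 − 1.645) = Φ(0.821) = 79.4%.

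A fixed design with pooled variance gives 79.2% and 79.9% after loss, and 86.5% and 87.1% if every randomized patient is analysed. The difference is about 0.6 to 0.7 percentage points throughout.

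**5. Effect on the looks.** If the stated counts of 282 and 564 were kept with a total of 864, the fractions would be 282/864 = 0.326 and 564/864 = 0.653. The one-sided z boundaries would change from 3.200, 2.141 and 1.695 to 3.238, 2.168 and 1.691, a negligible shift.

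**6. RNA substudy.** The abstract has 96 and three places in the body have 60. The difference is 36 patients (36/60 = 60%). The article contains no calculation for this number, so arithmetic cannot settle it.

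**The case against.** The strongest reply is that the body of the article leaves no doubt. There, 846 agrees with both arm sizes, both look counts and the dropout step. The 864 occurs once, in a summary, and looks like two transposed digits. The gap is 2.1%, the power difference is under one point, and a spending function tolerates small shifts in look timing. The RNA profiles are listed among other outcome measures and are excluded from the FAS and PPS analyses.

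Most of this stands, and it limits the point in three ways:
- A reader might infer that the interim fractions are in conflict. They are not: one-third and two-thirds appear in all three places.
- A reader might infer that the recruitment target is undefined. The methods define it coherently; it is the abstract that departs from them.
- A reader might want both totals replaced by 879, because neither leaves 703 evaluable patients after 20% loss (677 for 846, 691 for 864). That concerns the dropout inflation. It is a separate matter that would alter the design, and it is not needed to resolve this contradiction.

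The reply does not remove the contradiction. Transposition is only an inference, and it cannot explain 96 against 60. Nor can a difference between recruiting and randomizing explain the totals: the number randomized cannot exceed the number recruited, and the stated arms already sum to 846.

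**Conclusion.** The point holds as a reporting inconsistency. The abstract disagrees with the methods on the total (864 against 846, hence on the implied arm and look counts) and on the RNA substudy (96 against 60). Within the article 846 is the supported total; for the substudy, 60 is stated more often but is not derived.

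The effect on power is below one percentage point, assuming 45% against 55%, one-sided α = 0.05 and 20% loss. The primary inference is not threatened. The correction is still worth making, because the planned total is the reference for final enrolment and for any re-estimation, and recruitment was under way when the article was written.

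**What to change.** 1. Correct the abstract's total to 846, keeping arms of 564 and 282 and looks at 282 and 564. If another total is the intended one, state it in both places and recompute the arm and look counts from it.
2. Have the sponsor confirm the RNA substudy size and give that one number in the abstract, in both RNA rows of Table 1 and in the outcomes section.
3. Treat the shortfall against 703 evaluable patients as its own point, by restating the dropout-adjusted figure there.

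Item 2 and the correction to 846 in item 1 are text corrections and leave the conduct of the trial unchanged. Adopting a different total, or acting on item 3, would be a change of sample size and should be documented as such.

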**Discussion:**

This trial will provide high-quality evidence for DHI in treatment of AIS.

**Trial registration:**

Clinical Trials.gov NCT01677208 (Date of registration 22 December 2012).

**Electronic supplementary material:**

The online version of this article (doi:10.1186/s13063-015-1076-4) contains supplementary material, which is available to authorized users.

## Background

Acute ischemic stroke (AIS), characterized by an occlusion of the cerebral artery, is one of the leading causes of mortality, long-term disability, and morbidity. Thrombolytic therapy with intravenous tissue plasminogen activator (tPA), which remains the only therapeutic drug for AIS approved by the US Food and Drug Administration, is limited by the narrow time window of thrombolysis, bleeding complications, or high costs [1]. Other treatment strategies mainly utilize therapeutic agents to prevent or reduce cell damage from ischemia [2]. Hundreds of neuroprotective agents for ischemic stroke have reached clinical trials, but no optimal drugs for the clinical treatment of AIS have yet been developed [3]. This leads us to search for novel therapeutic approaches, and to investigate whether natural compounds extracted from herbs may be an alternative option to improve treatment for AIS [4].

Danhong injection (DHI), extracted from *Radix Salviae miltiorrhizae* (Danshen) and *Flos Carthami tinctorii* (Honghua), is a Chinese medicinal product approved by the China Food and Drug Administration (CFDA), and it is widely used in China for treating AIS [5]. Previous studies demonstrated the neuroprotective efficacy of DHI in rat models with cerebral ischemic-reperfusion injury [6, 7], and that the underlying pharmacological mechanisms might involve anti-inflammatory, anticoagulant, antithrombotic, antifibrinolytic, and antioxidant activities [8]. A number of clinical studies also supported the efficacy and safety of DHI in the management of AIS, but due to the methodological deficiencies of inadequate randomization, no double blinding, no placebo control, or incomplete outcome data, the quality of these studies was assessed as generally low [9]. There is a lack of critically appraised evidence such as well-designed randomized controlled trials (RCTs) to justify its clinical use and recommendation. Thus, we aim to investigate the efficacy and safety of DHI in the treatment of AIS in a well-designed, randomized, multicenter, double-blind and placebo-controlled trial. The trial was registered with an identifier (NCT01677208) in Clinical Trials.gov.

## Methods/Design

### Design

This is an adaptive design, multicenter, randomized, double-blind, placebo-controlled, superiority trial of DHI in the treatment of acute ischemic stroke. Eligible patients are randomly assigned in a 2:1 ratio into the DHI group or placebo control group (Fig. 1, Table 1). An adaptive design will be applied; if the superiority of DHI is observed at the time of the interim analysis, the trial can be terminated early.

**Fig. 1 Fig1:**
[figure not shown]
The flow diagram of this trial

**Table 1 Tab1:** Data collection schedule and measures

Period	Run-in period	Treatment period		Follow-up period		
Day	0	7 ± 2	14 ± 2	30 ± 5	60 ± 5	90 ± 3
Informed consent	×					
Inclusion/exclusion criteria	×					
Medical history	×					
UCG	×					
TOAST	×					
Medical examination	×	×	×	×	×	×
Concomitant medications	×	×	×	×	×	×
Outcomes						
BI scale	×	×	×	×	×	×
mRS scale	×	×	×	×	×	×
NIHSS	×	×	×	×	×	×
Chinese medicine symptom scales of “*Xueyu Zheng*”	×	×	×	×	×	×
EQ-5D scale	×	×	×	×	×	×
Global disability on mRS						×
New-onset major vascular events						×
Overall mortality						×
Incidence of severe hemorrhages						×
Incidence of moderate hemorrhages						×
AEs and SAEs						×
Profiles of microRNA in 60 patients from certain centers	×		×			×
Profiles of mRNA in 60 patients from certain centers	×		×			×

*UCG* ultrasound cardiogram, *TOAST* Trial of Org 10 172 in Acute Stroke Treatment, *BI* Barthel Index, *mRS* modified Rankin Scale, *NIHSS* National Institutes of Health Stroke Scale, *AEs* adverse events, *SAEs* serious adverse events, *microRNA* micro-ribonucleic acid, *mRNA* messenger ribonucleic acid

### Participant eligibility

To be fully eligible for participation in the trial, acute ischemic stroke inpatients must meet all of the following inclusion criteria and not meet any of the following exclusion criteria.

#### Inclusion criteria

Female or male inpatients.Aged 18–70 years.Clinical diagnosis of ischemic stroke causing a measurable neurological deficit defined as impairment of language, motor function, cognition and/or gaze, vision or neglect. Ischemic stroke is defined as an event characterized by the sudden onset of an acute focal neurologic deficit presumed to be due to cerebral ischemia after computed tomography (CT) scan excludes hemorrhage.Clinical diagnosis of “*Xueyu Zheng*” (blood stasis syndrome) defined as a total score of Chinese medicine symptom scales of “*Xueyu Zheng*” in ischemic stroke ≥20. The Chinese medicine symptom scales of “*Xueyu Zheng*” include the visual analogue scales (VAS) for the following items: (1) hemiplegia (0–10), (2) numbness of limbs (0–10), (3) dark face (0–9), (4) purple or dark lip (0–8), (5) rough skin (0–4), (6) pain with fixed point (0–5), (7) purple or dark tongue (0–10), (8) ecchymosis on the tongue (0–10), (9) purple sublingual vessels (0–10), (10) sublingual varices (0–8), (11) unsmooth pulse (0–8), and (12) intermittent pulse (0–1).Onset of symptoms within 1 week prior to initiation of study drug administration.Clinical diagnosis of cerebral anterior circulation obstruction.4 ≤ National Institutes of Health Stroke Scale (NIHSS) score <20.Patients willing to participate voluntarily and to sign a written informed consent document. Informed consent will be obtained from each patient or the subject’s legally authorized representative or relatives, or deferred where applicable, according to the regulatory and legal requirements of the participating centers.

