#### Exclusion criteria

Evidence of intracranial hemorrhage (ICH) or other cerebral diseases (e.g., vascular malformation, tumor, abscess or multiple sclerosis) on the CT or magnetic resonance imaging (MRI) scan.Patients who underwent thrombolysis or endovascular treatment.Known history of allergy or suspected allergy to the study drug.Fasting blood glucose <2.8 or >16.8 mmol/l or with severe complications due to diabetes (e.g., peripheral neuropathy, or diabetic gangrene).Liver function impairment with the value of alanine aminotransferase (ALT) or aspartate aminotransaminase (AST) over 1.5-fold the upper limit of normal range.Renal dysfunction with the value of serum creatinine over 1.5-fold the upper limit of normal range.Severe cardiac dysfunction on echocardiogram or the New York Heart Association (NYHA) heart functional class III or IV.History of prior stroke with a modified Rankin Scale (mRS) score ≥2.Atrial fibrillation complications.Severe stroke as assessed by appropriate imaging techniques (e.g., massive cerebral infarction affecting more than one lobe of the brain or over one-third of the blood-supply area of the middle cerebral artery).Legally disabled patients.Hemorrhagic tendency or severe or dangerous bleeding within the prior 3 months.Suspected alcohol addiction or drug abuse.Severe complications that would make the condition more complicated as assessed by the investigator.Women who are pregnant, lactating or have a positive pregnancy test, or women who plan to become pregnant in the subsequent 6 months.Women who have a menstrual period at baseline.Patients who are participating in other trials or have participated in other trials within the prior 3 months.

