### Outcome measures

#### Primary outcome

The primary outcome is the proportion of patients with a favorable outcome, defined as a score of 0–1 on the mRS [13] at day 90. The mRS is a commonly used scale for measuring the degree of disability or dependence in the daily activities of people who have suffered a stroke or other causes of neurological disability. The scale runs from 0–6, ranging from perfect health without symptoms to death.

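### Patients already at mRS 1 or BI ≥90 on day 0 are eligible, so both responder outcomes lose some sensitivity; stratifying the analysis on the day-0 score recovers part of it at no cost

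*Protocol article*

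**What the plan says.** All references are to the Protocol article.

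- **Inclusion criteria.** The current stroke must be one "causing a measurable neurological deficit defined as impairment of language, motor function, cognition and/or gaze, vision or neglect", with "4 ≤ National Institutes of Health Stroke Scale (NIHSS) score <20". Both conditions concern impairment.
- **Exclusion criteria.** The only mRS criterion is "History of prior stroke with a modified Rankin Scale (mRS) score ≥2". The other disability criterion is "Legally disabled patients". Both remove more disabled patients, and neither sets a minimum disability from the current stroke.
- **Primary outcome.** A favorable outcome is "defined as a score of 0–1 on the mRS [13] at day 90".
- **Secondary outcomes.** One is "The proportion of patients with the Barthel Index (BI) score of ≥90". Another counts an NIHSS improvement of at least 4 points or an NIHSS score of 0–1.
- **Table 1.** The mRS and the BI are both scored on day 0 and at every later visit.
- **Statistical analysis and Efficacy analysis.** The CMH test and logistic regression are among the listed methods. Factors that affect efficacy are to be taken into account, with age and gender as the examples.

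**The concern.** A responder outcome defined as a state, not a change, is informative only about patients who could move into or out of that state. A patient who is already at mRS 1 or BI ≥90 on day 0 and stays there is a success whichever arm he or she is in. Such patients add to both success rates and little to the difference. If there are many of them, the overall difference shrinks, or the 10-point difference used for sizing has to come from fewer patients.

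The NIHSS outcome does not have this problem. The entry floor of 4 means that nobody meets it on day 0, and improvement is counted from the patient's own starting value. The mRS and BI outcomes have no such protection, although the day-0 scores exist.

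**Working it through.** **1. Can a patient in the success state enter?** Entry needs a measurable deficit in any one listed domain, NIHSS 4–19 and a Xueyu Zheng score of at least 20.
- The Xueyu Zheng score does not require disability. Tongue colour, tongue ecchymosis and sublingual vessels alone can reach 10 + 10 + 10 = 30.
- The article describes the BI as measuring daily activities and mobility, whereas entry can rest on language, gaze, vision or neglect. BI ≥90 on day 0 is therefore not excluded.
- The Primary outcome section describes the bottom of the mRS as being without symptoms. That does not fit a required deficit with NIHSS ≥4, so the mRS gap is in effect mRS 1.

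**2. Reproducing the planned size.** Inputs from Sample size estimation and Interim analysis: 45% v 55%, 2:1 allocation, one-sided α = 0.05, power 80%, and looks at 1/3, 2/3 and the end with O'Brien-Fleming-type spending.
- Fixed design: N = [3(0.45)(0.55) + 1.5(0.55)(0.45)] × (1.645 + 0.842)² / 0.10² = 1.11375 × 6.183 / 0.01 = 688.6.
- The boundaries are z = 3.200, 2.141 and 1.695, and the inflation factor is 1.0203.
- 688.6 × 1.0203 = 702.6, which matches the stated 703.

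**3. Dilution model (assumed).** A share f is in the success state on day 0, and 95% of these are still there at day 90 in both arms. The rest respond at 45% v 55%.
- p_C = 0.95f + 0.45(1 − f) and p_T = 0.95f + 0.55(1 − f), so Δ = 0.10(1 − f).
- SE² = [3 p_C(1 − p_C) + 1.5 p_T(1 − p_T)] / 703.
- Power is the chance that a statistic with final mean Δ/SE crosses the boundaries above.

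**4. Same model, stratified on day-0 status.** Δ is unchanged, but the variance is now taken within strata: SE² = [(1 − f) × 1.11375 + f × 4.5 × 0.95 × 0.05] / 703.

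| f | p_C / p_T | Δ (points) | SE, Δ/SE, power: unstratified | SE, Δ/SE, power: stratified |
|---|---|---|---|---|
| 0 | 45.0 / 55.0% | 10.0 | 0.0398, 2.512, 80.0% | same |
| 5% | 47.5 / 57.0% | 9.5 | 0.0398, 2.385, 76.3% | 0.0390, 2.437, 77.8% |
| 10% | 50.0 / 59.0% | 9.0 | 0.0398, 2.262, 72.4% | 0.0382, 2.358, 75.5% |
| 20% | 55.0 / 63.0% | 8.0 | 0.0394, 2.030, 64.1% | 0.0364, 2.195, 70.1% |

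**5. The other reading of the planning rates.** Suppose 45% and 55% describe the whole trial population, such patients included. The overall difference is then still 10 points and unstratified power is still 80.0%. Only the difference needed in the rest rises, to 0.10/(1 − f): 10.5, 11.1 and 12.5 points at f = 5%, 10% and 20%.

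Stratifying helps here too. At f = 10% the rest respond at (0.45 − 0.095)/0.9 = 39.4% v (0.55 − 0.095)/0.9 = 50.6%. Then SE² = [0.9 × (3 × 0.394 × 0.606 + 1.5 × 0.506 × 0.494) + 0.1 × 0.21375] / 703, so SE = 0.0378, Δ/SE = 2.65 and power is about 83.5%.

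**The case against.** The case against is substantial, and most of it stands.

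- **The share is unknown.** The article gives no day-0 distribution of mRS or BI. The values of f are illustrations, and for the mRS the share may be small. This stands.
- **The stated power may be right.** A reader might infer that the trial has less than 80% power. The documents do not support that: Sample size estimation gives 45% for patients on placebo plus standard care and a 10-point increase for the DHI group, which is most naturally read as the whole population (step 5).
- **These patients are not certain successes.** A reader might infer that they succeed regardless of treatment. Success is judged at day 90, and such patients can worsen, have a new event or die. DHI could in principle prevent some of that. The 95% in both arms is a modelling assumption.
- **There is no bias.** Eligibility is the same in both randomised arms. The cost is sensitivity only.
- **There is already a severity floor.** Inpatient status, a measurable deficit and NIHSS ≥4 keep out the mildest cases and practically rule out mRS 0. This narrows the gap without closing it.
- **Adjustment is foreseen in general terms.** The article names the CMH test, logistic regression and covariates, and an article may leave the exact list to the analysis plan. The absence of day-0 mRS and BI from the examples is therefore not an error. It does leave room to name them.

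**Conclusion.** The point holds as a modest loss of sensitivity. Nothing in the eligibility sections keeps out a patient already at mRS 1 or BI ≥90 on day 0, and both outcomes are absolute states. The size cannot be fixed from the article. On the assumed model with N = 703, stratifying raises power from about 72% to 75% at a share of 10%, and from about 64% to 70% at 20%. At 5% the gain is under 2 points. If the planning rates already include such patients, there is no shortfall against the stated power, and stratifying still adds precision.

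It might seem to follow that these patients should be excluded. The documents do not carry that. With recruitment under way, a changed criterion would put two entry populations into one trial to cure a loss of unknown size. Part of that loss can be recovered in the analysis.

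**What to change.** - Leave the eligibility criteria as they are.
- Analyse BI ≥90 by a CMH test stratified by day-0 BI (≥90 v <90).
- Adjust the primary mRS 0–1 comparison for day-0 mRS, either by a CMH test stratified in the same way (0–1 v 2 or more) or by adding day-0 mRS to the logistic model in Efficacy analysis.
- Fix the choice before any comparison by arm is seen, and use the same statistic at both interim analyses and at the end.
- Report the number and share of patients at mRS 0–1 and at BI ≥90 on day 0, by arm.

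The change needs no new data, visit or method, since Table 1 already collects both scores and the tests are already named. The only cost is the text that specifies it. It recovers part of the lost sensitivity, not all: in the table, stratified power at f = 10% or 20% is still below 80%, because stratifying cannot create a treatment contrast among patients who are already in the success state.
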